##### Sequential assessment of cognition and psychomotor development

2.4.2.2.

Precursors to cognitive development will be assessed at 15 months corrected age using the “Batterie d’Évaluation Cognitive et Socio-émotionnelle” (58). This psychometric tool assesses cognitive and socio-emotional development in young children up to 24 months, based on standardized activities and standardized sequences of interactions between the psychologist and the child.

Child development at 2 and 4 years will be measured using the Ages and Stages Questionnaire (ASQ 24 and ASQ 48) (59). Those questionnaires, filled by parents, include 30 items assessing five areas of development: communication, gross motor skills, fine motor skills, problem solving, and individual or social skills. A French, validated translation is available, featuring age-appropriate questions corresponding to the child's expected level of development and normative data.

Cognitive and social development will be assessed at 6 years using an extensive set of neuropsychological tests and theory of mind tasks: 1/Global intellectual abilities will be assessed with the Wechsler Intelligence Scale for Children (WISC-V). This scale has five main indices: Verbal Comprehension, Visual Spatial, Fluid Reasoning, Working Memory, and Processing Speed and allows calculation of a global intellectual quotient. 2/To assess attention, inhibition and mental flexibility, The NEPSY's Auditory Attention and Associated Responses subtest will performed (60). 3/The NEPSY's Sentence Repetition subtest will be used to assesses phonological working memory abilities through a task where participants have to repeat sentences of increasing length and complexity (60). 4/The Test of Everyday Attention for Children (TEA-CH)'s Opposite Worlds subtest will attention and inhibition abilities through a pointing task in response to a verbal cue (61). 5/The Raven Matrix Test assesses nonverbal intellectual efficiency through a reasoning by analogy task (62). 6/Social cognition will be assessed using Cognitive and Affective theory of mind abilities tasks (63–69).

##### Parental anxiety and depressive symptoms

2.4.2.3.

Anxiety and depressive symptoms will be assessed in both parents at 7 weeks ± 1 after birth. Maternal anxiety and depressive symptoms will be measured using the State Trait Anxiety Inventory (STAI-Y), Parental Stress Index (PSI), Beck Depression Inventory (BDI), Edinburgh Postnatal Depression Scale, and Modified Perinatal Post Traumatic Stress Disorder Questionnaire. As some of these scales are not suitable for rating fathers, they will be replaced with non-gender specific scales. Paternal anxiety and depressive symptoms will therefore be measured using the STAI-Y, PSI, BDI, and Posttraumatic Stress Disorder Checklist for DSM-5 (70–75).

### Data analysis

2.5.

First, we will carry out a descriptive analysis of the data, with means and standard deviations, and counts and percentage for the quantitative and qualitative variables, respectively. For all subsequent analysis, the group (experimental vs. control) will be the independent variable. The scores obtained on each scale will be the dependent variable.

#### Statistical analysis of primary outcome

2.5.1.

The main judgment criteria (score in the “child's social engagement” dimension of the CIB at 12 months) will be compared between the experimental group and the control group using a Student or Mann-Whitney test, depending on the application conditions.

Secondary judgment criteria (scores in the other dimensions of the CIB at 12 months) will be compared between the experimental group and the control group using a Student or Mann-Whitney test, depending on the application conditions.

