### Background

1.1.

In 2018, the World Health Organization (WHO) estimated that 15 million children are born prematurely each year worldwide. The number of newborns surviving a premature birth has gradually increased over the years (1, 2). However, many of those will exhibit varying degree of neurological impairment. In the recent decades, the clinical and morphological picture of brain insults due to prematurity has changed. Classically, extensive clastic injuries (e.g., cystic necrosis of white matter, large infarction of brain parenchyma) most often led to cerebral palsy and/or moderate to severe cognitive impairment. Since the 1990s, however, their incidence has dwindled, and they have been supplanted by less prominent and more diffuse brain damage leading to the loss of vulnerable cells and impaired brain development (3–5).

Nowadays, the spectrum of neurodevelopmental outcomes of preterm babies broadly includes deficits in language, gross and fine motor skills, behavior, and cognition (especially executive functions and social cognition). The severity of the clinical picture is related to the degree of prematurity (6–12). Many brain areas undergo a sensitive period of development during the third trimester of gestation and after birth, during which sensory input shapes neurological maturation and future function. This is the case of the median prefrontal cortex, temporoparietal junction and posterior temporal sulcus (involved in cognition and social cognition) (13–15), the cerebellum, as well as visual, olfactory and somatosensory pathways (16). Premature birth dramatically modifies the context of this developmental window. During hospitalization, the developing brains of infants born preterm are exposed to stimuli that may be detrimental to their maturation (17) with either too much or too little sensorial input (18). This is referred to as *dystimulation*.

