#### Study population

2.2.1.

Children born between very preterm and their parents will be eligible if they meet the following inclusion criteria: 1/the child is inborn, 2/birth between 25 and 32 weeks of gestation and weight over 600 g at birth, 3/the child's hospitalization at the recruiting center is planned until 36 weeks corrected age, 4/the child's parents have parental authority and have agreed to participate in the study by signing the informed consent, 5/the child's parents are available physically and mentally to participate in the study and 6/the child and his/her parents are affiliated to the social security system.

The exclusion criteria are the following: 1/the child is hemodynamically unstable, 2/the child has a suspected comorbidity (e.g., genetic syndrome, congenital malformation, brain injury, skin pathology), 3/the child was born from a multiple pregnancy, 4/the child was born anonymously, 5/the child is to be separated from his/her parents (e.g., assigned to infancy protection services).

If the child's condition does not allow the practice of STS (for example: hemodynamic compromise, enterocolitis), the intervention may be temporarily discontinued until the condition improves. The discontinuation and the resumption of the intervention are decided by the medical staff in charge of the child, who informs and explains the decision to the parents. Newborns will not be excluded from the intervention group.

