#### Sample size calculation

2.2.2.

The sample size has been calculated so that a two-tailed test will detect a significant difference in the primary endpoint (Coding infant behavior scale at 12 months corrected age, see below), with a power of 90% and a significance level of 0.05 (alpha value). Forty-eight infants would be required in each group (NQuery 4.0® software). In anticipation of loss to follow-up, the target size has been increased by 20%, such that 60 children will be included in each group, resulting in inclusion of a total of 120 infants.

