Parents will be coached by a trained, designated professional, initially using a mannequin. They will also be shown a training video and given an illustrated training booklet covering all the steps of STS. They will begin from the 10th day after birth and when the parents feel ready to perform it and will continue until discharge from hospital or 36 weeks corrected age. STS should be carried out 5 times per week, 5-15 min each time. STS will be performed when the newborn exhibits quiet alertness (State 3 or 4 according to Brazelton (50)). The intervention will be interrupted if signs of discomfort are detected in the newborn or his/her parents. Once a week, a trained psychologist or psychomotor therapist will supervise the parent's gestures and discuss his/her experience.

“Skin to skin care” will be practiced without any restriction in both groups, following local policies. In the experimental group, newborns and their parents will participate in STS in addition to kangaroo care. The time, number, duration of each skin-to-skin care or STS will be collected, as well as somatic stability, initial and maximal state of alertness of the baby (51).

Preterm babies will benefit from the usual neonatal intensive care, following the local policies of each center.

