#### Primary outcome

2.4.1.

The quality of interactions between the very premature infants and their parents will be scored at 12 months corrected age using the Coding Infant Behavior system (CIB) (52). The latter assesses the quality of child-parent interactions by observing the occurrence of behaviors along six dimensions: parental sensitivity, parental intrusion, child's social engagement, child's negative emotionality and engagement, dyadic reciprocity, and negative dyad states. This scale is validated from birth to 3 years of age and has shown a great sensitivity in scoring interactions in many social and/or pathological situations (53). Early CIB scores have previously been correlated with cognitive development (54). We will record two 15 min sequences of child-parent interactions during free play. Observations will be double-quoted by professionals trained to use the CIB, blinded to the randomization group. The main judgment criteria will be the score in “child's social engagement” dimension of the CIB system. The Secondary judgment criteria will be the scores in the other dimensions of the CIB system.

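### The primary score is compared by an unadjusted two-group test; prespecified adjustment for gestational age and centre would be more efficient if these are prognostic, and would remove chance imbalance from the estimate

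*Protocol article*

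**What the plan says.** The endpoint is fixed in the protocol article under Primary outcome: "The main judgment criteria will be the score in “child's social engagement” dimension of the CIB system". Under Statistical analysis of primary outcome, this score is to be "compared between the experimental group and the control group using a Student or Mann-Whitney test", the choice depending on whether the test's conditions are met. The Data analysis section sets the frame for everything after the descriptive summary: "For all subsequent analysis, the group (experimental vs. control) will be the independent variable". No covariate, centre term or adjusted sensitivity analysis is named.

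Four other places bear on the choice:

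- Study population admits infants with "birth between 25 and 32 weeks of gestation and weight over 600 g at birth". They must also be inborn, so birth centre and gestational age are both known before randomisation.
- Background states: "The severity of the clinical picture is related to the degree of prematurity".
- Design describes a multicentre trial.
- Intervention says "Preterm babies will benefit from the usual neonatal intensive care, following the local policies of each center", and skin-to-skin care, which is the comparator, likewise follows local policy.

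**The concern.** Neither test named for the primary endpoint has room for a covariate. Any variation in the score due to gestational age or centre therefore stays in the residual, and the standard error is larger than it need be. In a trial of this size the arms may also differ by chance in gestational age or centre mix. An unadjusted comparison carries such a difference into the observed estimate. Adding covariates after an imbalance has been seen would be data-driven, so the decision has to be made beforehand.

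At stake are some power, the width of the interval, and how the result reads if the arms turn out unlike. The validity of the test is not at stake.

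**Working it through.** **Inputs.** From Sample size calculation: two-sided alpha 0.05, power 90%, 48 evaluable infants per group, 20% loss, 60 per group. Not in the document: the difference to be detected, the SD, and the share of outcome variance (R²) explained by gestational age and centre. R² is therefore an assumption, taken from 0.02 to 0.20.

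**Step 1: the plan's own figures.** The inflation reproduces: 48 / (1 − 0.20) = 60 per group, 120 in total. The 48 itself cannot be reproduced without a difference and SD, so I solved backwards. By the normal approximation, d = √(2/48) × (1.960 + 1.282) = 0.662. With the noncentral t distribution on 94 degrees of freedom, d = 0.669.

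**Step 2: power after adjustment.** Adjustment reduces the residual SD by the factor √(1 − R²), so the effective standardised difference is 0.669 / √(1 − R²). With 48 per arm:

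| Assumed R² | Effective d | Power | Interval narrower by | Per arm for 90% power |
|---|---|---|---|---|
| 0 (unadjusted) | 0.669 | 90.0% | – | 48 |
| 0.02 | 0.675 | 90.6% | 1.0% | 48 |
| 0.05 | 0.686 | 91.4% | 2.5% | 46 |
| 0.10 | 0.705 | 92.7% | 5.1% | 44 |
| 0.20 | 0.747 | 95.2% | 10.6% | 39 |

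**Step 3: cost of the covariates.** Five covariate terms leave 89 residual degrees of freedom instead of 94. That alone costs less than 0.1 power point in every row.

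The table takes the covariates as balanced between arms. Under simple randomisation they are not exactly balanced, and for roughly normal covariates the expected variance of the adjusted estimate rises by the factor 1 + q/(N − q − 3), with q terms and N = 96.

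- For gestational age alone: 1 + 1/92 = 1.011, so the gain starts above R² = 1 − 1/1.011, about 0.01.
- For five terms: 1 + 5/88 = 1.057, so it starts above about 0.05. At R² of 0.10 and 0.20 the power is then about 91.3% and 94.1%.

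The case for adjustment is thus firmest with gestational age plus few centre terms.

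**Step 4: chance imbalance.** The standard error of the between-arm difference in a covariate's mean is √(2/48) = 0.204 covariate SD, so 95% of randomisations fall within 1.96 × 0.204 = 0.40 SD. The resulting shift in the outcome is 0.40 × √R². For R² of 0.05, 0.10 and 0.20 this is up to 0.09, 0.13 and 0.18 outcome SD, or 13%, 19% and 27% of the 0.669 SD difference.

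**The case against.** The strongest reply is that nothing here is an error. Under the simple random assignment that the Randomization section describes, the unadjusted comparison keeps its type I error, is unbiased over repeated randomisations, and has an interval with correct coverage. Its standard error already allows for chance imbalance. This stands in full: adjustment is an improvement in efficiency.

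A second reply is that covariates are often left to the full protocol or analysis plan, and that naming group as the independent variable may only identify the factor of interest. This limits the point but does not remove it. The article goes beyond silence by naming specific tests that take no covariates.

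Four stronger readings are tempting, and the document does not support them:

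- **That the protocol itself calls both factors influential.** Background ties prematurity to the severity of neurodevelopmental deficits, not to the CIB score. For centre, the text says only that care follows local policy; an effect on outcome is an inference.
- **That the interval is too wide.** It could be narrower, but it is not wrong.
- **That the unadjusted test is conservative because randomisation is stratified.** No stratification factor is stated.
- **That gestational age must be adjusted for because it sets exposure to the intervention.** The longest possible window, (36 − GA) × 7 − 10 days, is 67 days at 25 weeks and 18 days at 32 weeks. These are upper bounds, since the start also depends on the parents' readiness, the intervention may end at discharge, and it may be paused. Only the experimental arm is exposed, so this concerns an effect that may vary with gestational age, which a main-effect term does not address.

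**Conclusion.** The point holds as a recommendation on efficiency. The document fixes an unadjusted primary test although two pre-randomisation factors that are plausibly prognostic are at hand. The gain ranges from about half a power point at R² = 0.02 to about five points at R² = 0.20, before the small allowance for covariate imbalance in step 3. The more practical benefit is that a chance difference in gestational age or centre mix would no longer sit in the estimate.

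These sizes rest on two things the document does not give: the R², which is assumed, and the 0.669 SD, which is back-solved from 48 per arm. If neither factor is related to the CIB score, nothing worthwhile is gained.

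**What to change.** Prespecify as the primary analysis a linear model of the CIB child's social engagement score on group, gestational age at birth as a continuous variable, and centre, with small centres pooled or centre as a random effect so that few terms are spent on it. Report the adjusted mean difference with its 95% confidence interval. State that robust or bootstrap standard errors will be used if the residuals are clearly non-normal; this covers the situation for which the plan now turns to Mann-Whitney. Keep the unadjusted Student or Mann-Whitney comparison as a sensitivity analysis.

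The change is one of wording, made before outcome data are seen. It needs no extra infants or visits, and both covariates are known at birth. The price is a few degrees of freedom (under about 0.1 power point for five terms) plus the modest variance cost in step 3. The number of centres is not given, so the number of centre terms should be settled once it is known.

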#### Statistical analysis of secondary outcomes

2.5.2.

All secondary outcomes are quantitative measures. For all these measures, we will compare the scores of the experimental group with those of the control group, according to the distribution of the data, with parametric or nonparametric tests (Student's *t*, Mann-Whitney, chi^2^ or Fisher's exact tests), depending on the application conditions. Correlations will be calculated between quantitative measures.

A *p* value of < 0.05 will be considered statistically significant.

Statistical analysis will be performed with software “R®”(76).

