##### Morphological and functional development of the brain

2.4.2.1.

All the data yielded by the following paraclinical examinations will be anonymized and sent to the main investigating center for centralized review. They will be interpreted by two experts for each technique used, blinded to the randomization group.

Serial cerebral ultrasound scans will be performed during the infants' NICU stay, following a standardized protocol. Lesions will be classified: 1/according to the Papille classification for intraventricular hemorrhages, 2/according to the De Vries classification for periventricular leukomalacia (55). Moreover, several two-dimensional measurements will be performed on ultrasound scan to assess brain growth: interhemispheric distance, ventricular width, thickness of motor and somatosensory cortex, diameter of thalami and cerebellum.

Brain magnetic resonance imaging (MRI) will be performed at term-corrected age including a diffusion sequence, following a standardized protocol of acquisition. Imaging will be interpreted according to Kidokoro (56). Moreover, regional brain volumes will be quantified using semi-automatic, post-hoc segmentation.

EEG and amplitude-integrated EEG will be sequentially recorded. Timing of the EEG recordings and their interpretation will follow the guidelines of the French society of electrophysiology (57).

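### Section 2.5.2 calls every secondary outcome quantitative, and its group-only two-sample tests do not use the serial structure of the brain-maturation outcomes

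*Protocol article*

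**What the plan says.** Section 2.5.2 opens with "All secondary outcomes are quantitative measures". It then says the two arms will be compared on all of these measures "with parametric or nonparametric tests (Student's *t*, Mann-Whitney, chi^2^ or Fisher's exact tests), depending on the application conditions". Section 2.5 makes group the independent variable, and the score on each scale the dependent variable, in every analysis after the descriptive one. No other explanatory variable is named.

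Section 2.4.2.1 sets out the brain outcomes to which this rule applies:

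- Ultrasound is repeated during the NICU stay. "Lesions will be classified": "according to the Papille classification for intraventricular hemorrhages" and "according to the De Vries classification for periventricular leukomalacia".
- The same scans supply several linear dimensions intended to show brain growth.
- "EEG and amplitude-integrated EEG will be sequentially recorded".
- MRI is done at term-corrected age.

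Section 2.2.1 admits infants born at 25 to 32 weeks. Section 2.3 starts STS no earlier than the 10th day after birth.

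**The concern.** There are two separate problems.

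The first is factual. A lesion grade is an ordered class, not a quantity. Section 2.5 itself foresees qualitative variables ("with means and standard deviations, and counts and percentage for the quantitative and qualitative variables, respectively"), and chi-square and Fisher tests would have no role if everything were quantitative.

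The second matters more. The abstract describes brain maturation as assessed sequentially, so the scientific question concerns change over time. None of the four listed tests has a place for time, for several values from one infant, or for a covariate. Unless the series is first reduced to one value per infant, which the article does not mention, the analyst must either pick one time point and discard the rest, or test each time point in turn. The first loses power and the second multiplies tests. Gestational age at birth and corrected age at recording, both likely to explain much of the variation in brain dimensions, stay in the error term.

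**Working it through.** **The plan's own figure.** Section 2.2.2 gives 48 per group, raised for 20% loss: 48 / (1 − 0.20) = 60 per group, 120 in total. This reproduces. It concerns the primary endpoint; no figure is given for the secondary outcomes. The 48 cannot be re-derived because no effect size is stated (at 90% power and two-sided 0.05 it corresponds to about 0.67 SD).

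**Lesion grades under the listed tests.** Simulation with 60 per arm, a five-level grade and 3,000 runs per scenario. The control distributions and odds ratio are assumptions.

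| Control distribution (%) | Odds ratio | t | Mann-Whitney | Chi-square on grades | Fisher any/none |
|---|---|---|---|---|---|
| 75/12/7/4/2 | 1 | 4.1% | 4.0% | 3.2% | 2.5% |
| 75/12/7/4/2 | 2.5 | 41% | 48% | 25% | 38% |
| 50/20/15/10/5 | 1 | 4.8% | 4.6% | 4.0% | 3.4% |
| 50/20/15/10/5 | 2.5 | 67% | 72% | 47% | 62% |

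With no group difference (odds ratio 1), no test exceeds 5%. The choice affects power only: with odds ratio 2.5, the unordered chi-square is 23 to 25 points below Mann-Whitney.

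**One serial quantitative measure.** Inputs: 48 per arm (section 2.2.2), two-sided 0.05 (sections 2.2.2 and 2.5.2). Assumed, because the article gives none of them: a constant difference of 0.5 SD, m = 3 to 5 recordings, equal correlation ρ = 0.3 to 0.7 between recordings.

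- One time point: power = Φ(0.5 × √(48/2) − 1.96) = Φ(0.489) = 69%.
- Mean of m recordings: variance factor V = (1 + (m − 1)ρ)/m, power = Φ(0.5 × √24/√V − 1.96).
- Each time point tested at 0.05: chance of at least one false positive, by simulation of m correlated normal statistics.
- Recordings pooled as if independent: error = 2 × (1 − Φ(1.96/√(1 + (m − 1)ρ))).

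| m | ρ | V | Power, mean | Error, separate tests | Error if pooled |
|---|---|---|---|---|---|
| 3 | 0.3 | 0.533 | 92% | 13.6% | 12.1% |
| 3 | 0.5 | 0.667 | 85% | 12.5% | 16.6% |
| 3 | 0.7 | 0.800 | 78% | 11.0% | 20.6% |
| 4 | 0.3 | 0.475 | 94% | 17.5% | 15.5% |
| 4 | 0.5 | 0.625 | 87% | 15.6% | 21.5% |
| 4 | 0.7 | 0.775 | 80% | 12.8% | 26.6% |
| 5 | 0.3 | 0.440 | 96% | 20.9% | 18.6% |
| 5 | 0.5 | 0.600 | 88% | 18.2% | 25.8% |
| 5 | 0.7 | 0.760 | 80% | 14.8% | 31.5% |

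The per-infant mean stands in here for an analysis that uses the whole series; the mixed model itself was not simulated. The constant difference favours the mean, so a difference that emerges only late would narrow the gap to a late single time point. Each row concerns one measure.

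**Spread in age and exposure.** Entry at 25 to 32 weeks means that recordings at one postnatal day could differ by 32 − 25 = 7 weeks of corrected age. If STS ran from day 10 (1.4 weeks) to 36 weeks, possible exposure would be 36 − 25 − 1.4 = 9.6 weeks for the most immature infants and 36 − 32 − 1.4 = 2.6 weeks for the most mature.

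**The case against.** The strongest reply is that the rule is valid as it stands, and much of that reply is right.

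- *Lesions.* A reader might infer that lesion grades will be wrongly tested. The text does not support this: Mann-Whitney suits ordered grades, Fisher suits presence or absence, and both are listed. Only the sentence is wrong.
- *Serial data.* A reader might infer that repeated recordings will be pooled as independent, with the error rates in the last column above. The article nowhere says so. A two-sample test on one value per infant (a mean, a slope, a change, or a recording at a fixed corrected age) is valid.
- *Corrected age.* MRI is fixed at term-corrected age, ultrasound follows a standard protocol, and EEG timing follows a national guideline. Those schedules are not shown, so it cannot be claimed that infants will in fact be compared at different ages.
- *Findings before STS.* A reader might infer that early lesions will be credited to treatment. Suspected brain injury is an exclusion, randomisation balances the remainder in expectation, and no text says that scans before day 10 count as outcomes. Counting them would dilute a difference rather than bias it.
- *Scope.* How repeated measures are summarised is often left to the full protocol or analysis plan, neither of which is shown.

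The scope argument does not dispose of the point. Sections 2.5 and 2.5.2 are not silent: they state a single analysis for all secondary outcomes, with group as the sole independent variable, and that stated analysis fits a growth endpoint poorly.

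**Conclusion.** The opening sentence of section 2.5.2 is wrong on the document's own text; by itself this is a minor correction. The stated rule is not invalid, but it is poorly matched to serial ultrasound and EEG/aEEG measures of maturation. Applied one time point at a time, it gives 69% power against 78% to 96% for a per-infant mean, or a familywise error of 11% to 21% per measure if every time point is tested. Both ranges rest on the assumed 0.5 SD difference, 3 to 5 recordings, correlation 0.3 to 0.7 and 48 per arm. In hospital, up to 60 per arm may be available; one time point would then give Φ(0.5 × √30 − 1.96) = 78%, so the loss would be smaller.

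The documents do not support the stronger conclusion that the trial's secondary tests will have inflated error. The pooled-data figures of 12% to 32% describe a practice that the text does not prescribe. The primary analysis is not touched.

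**What to change.** 1. Delete or correct the sentence in section 2.5.2. State for each secondary outcome whether it is quantitative, ordinal or categorical, and which analysis it receives.
2. Analyse haemorrhage and leukomalacia grades as ordinal or categorical: Mann-Whitney or proportional odds for ordered grades, Fisher for presence or absence. Avoid an unordered chi-square on the grades.
3. Analyse serial ultrasound dimensions and quantitative EEG/aEEG scores with a linear mixed model: group, corrected age at recording, group × corrected age, gestational age at birth, and a random infant effect. Say in advance which contrast is tested (the interaction, or the group difference at a named corrected age).
4. Count as outcomes only recordings after a time origin defined identically in both arms; day 10, the earliest stated start of STS, is a natural choice. Use an earlier recording as a baseline covariate where one is available. The article does not show that every infant will have one, so the model must not depend on it.

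The cost is wording, modest extra programming, and an assumption about the shape of growth over time (linear or otherwise), which should be checked. The core model uses recordings and birth data that the trial already collects. The change should be fixed before any unblinded analysis.
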